### Data collection

Evaluations will be conducted by a specialist physician with >25 years’ experience at three time points: at baseline (t0) and at 6 months (t1) and 12 months (t2) post-intervention. Evaluations will be carried out in single sessions at Granada University School of Medicine except for the fMRI scan, which will be performed at the Mind, Brain, and Behavior Research Center of the University of Granada by technical staff at this center. (Fig 1).

Data will be collected on the following clinical and sociodemographic variables: age, sex, type of stroke, date of stroke, interval between stroke and treatment, gait capacity on the Functional Ambulation Classification (FAC) scale [40], upper limb lesion (functional or hygienic), cognitive status [41], family support, need for assistance (Barthel index) [42], and anesthetic risk (ASA) [43], classifying upper limb lesions as functional or hygienic hand and categorizing elbow, wrist, and hand deformities according to Keenan et al [33].

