#### Functionality evaluation (main variable).

This evaluation will be performed at each time point (0, 6, and 12 months) using the following instruments:

1. Modified Ashworth spasticity scale [32], which measures the degree of spasticity from 0 to 5. Significant improvement at one or more of the five evaluated sites (elbow, forearm, wrist, thumb, fingers) will be considered a positive outcome.2. Hand function scale by House et al. [28], which considers nine functional grades.3. Zancolli hand classification [31].4. Fugl-Meyer scale for post-stroke recovery. It includes 33 items scored from 0 to 2 and a scale for shoulder-wrist and wrist-hand domains scored from 0 to 66 [29].5. VAS, which provides a subjective estimate of pain, using a line ranging from 0 “no pain” to 10 “worst pain imaginable” [34].

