#### Evaluation of health costs.

Health resources consumed by participants will be calculated in accordance with an economic model developed to compare surgical treatment with botulinum toxin alone in the Spanish setting. Clinical records will be reviewed to gather data on medication, specialist visits, primary health care consultations, and health transportation. Prices in the Pharmaceutical School Council Catalog will be applied to medications. Information in the Spanish eSalud health cost database will be used to generate a unitary cost for primary and specialized care consultations, emergencies (hospital and primary care), and health transportation. Hospitalization costs will be based on mean values published by the Ministry of Health, Social Policy, and Equality for the corresponding diagnostic groups. Account will also be taken of the need for occupational therapy. Costs of the main caregiver and secondary caregivers will be based on the hours they devote to care activities, applying the market hourly rate for similar services. In addition, a cost-utility analysis will be performed based on patient-reported quality-of-life results.

Outcome measures are summarized in Table 2.

**Table 2 pone.0322588.t002:** Summary of outcome measures. GAS: Goal Attainment Scale; HADS: Hospital Anxiety and Depression Scale; MRI: Magnetic Resonance Imaging; PSQI: Pittsburgh Sleep Quality Index; SF-36: 36-item Short Form Survey.

Outcomes	Time point	Measurement definition
Change in functional and hygienic status of the affected upper limb	6 and 12 months	Measured using House, Keenan, Zancolli, Fugl Meyer, GAS, Asworth and VAS scales
Change in quality of life	6 and 12 months	Measured using SF 36 and New Castle Stroke-Specific quality of life scale
Changes in sleep quality	6 and 12 months	Measured using the PSQI
Changes in anxiety and depression	6 and 12 months	Measured using HADS score
Changes in caregiver burden	6 and 12 months	Measured using Carer Burden and Zarit scales
Changes in brain structure	6 and 12 months	Measured using MRI
Changes in brain function	6 and 12 months	Measured using fMRI
Treatment costs	12 months	Using model to simulate costs and quality-adjusted life years. Unit costs from published Spanish sources

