### Data analysis

The Student’s t-test will be used for between-group comparisons of continuous variables, applying the Mann-Whitney U test when the distribution is non-normal. Repeated-measures regression analysis will be conducted for within-group comparisons between follow-up visits and baseline. McNemar’s Chi-square test or Fisher’s exact test will be used for between-group comparisons of discrete variables (e.g., Ashworth spasticity scale or Caregiver Burden Scale) and McNemar’s Chi-square test for within-group comparisons. Pearson’s correlation coefficient analysis will be applied to evaluate relationships between functional scores and the results of health, anxiety-depression, and sleep quality questionnaires. Multivariate linear regression will be performed to determine whether the functional improvement behaves as an independent variable with significant influence on aspects of psychosocial quality of life.

The fMRI results will be expressed descriptively and submitted to correlation analysis. The corrected BOLD response associated with the upper limb movement will be analyzed using a general linear model in SPM8, considering the aforementioned confounders and independent variables. The regression coefficients obtained for each patient will be analyzed by ANOVA to identify the brain regions that manifest effects associated with the variables of interest. Multiple comparison correction criteria will be applied for statistical decisions, resulting in an alpha error rate ≤0.05 throughout the trial.

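### The clinical scales are compared between arms without baseline as a covariate, and the repeated-measures model is used only within arms: valid, but inefficient

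*Protocol article*

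**What the plan says.** The Data analysis section gives each method a role.

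- Between arms, continuous variables: "t-test will be used for between-group comparisons of continuous variables, applying the Mann-Whitney U test when the distribution is non-normal". No covariate is named, and the section does not say whether the tested value is the change from baseline or the score at the visit.
- Between arms, discrete variables: McNemar's or Fisher's test, with the Ashworth and Caregiver Burden scales as examples.
- Within arms: "Repeated-measures regression analysis will be conducted for within-group comparisons between follow-up visits and baseline", and for discrete variables McNemar's "Chi-square test for within-group comparisons".
- The one multivariable regression on clinical data has another purpose: "Multivariate linear regression will be performed to determine whether the functional improvement behaves as an independent variable" with influence on psychosocial quality of life. It does not estimate the effect of surgery against toxin. Confounders are mentioned only for the fMRI model.

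Baseline is measured for the main variable and the other clinical scales. For functionality: "This evaluation will be performed at each time point (0, 6, and 12 months) using the following instruments". Tables 1 and 2 word the outcomes as changes at 6 and 12 months, for example "Change in functional and hygienic status of the affected upper limb". Data collection also records limb type, "classifying upper limb lesions as functional or hygienic hand".

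**The concern.** The primary aim is a comparison of surgery with botulinum toxin, in 44 patients whom the Discussion expects to differ in baseline injury and limb sequelae. The Randomization section describes no stratification. In a trial of this size some chance imbalance at baseline is likely, and precision is scarce. A patient's own baseline score is usually the cheapest source of precision, and it will already have been collected.

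The plan has a model suited to three visits but applies it where it cannot compare treatments. The randomised comparison is left to a two-sample test that cannot adjust for baseline. If that test is run on follow-up values, baseline does not enter at all. If it is run on change, baseline enters by plain subtraction, which costs power when the correlation between baseline and follow-up is modest. At stake is the width of the interval for the treatment effect and how far the estimate is exposed to chance imbalance.

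**Working it through.** **Inputs.** From the sample-size paragraph under Participants: 5% type I error, 80% power, 0.8 SD, k = 2, f = 0.5, n = 16.71472, 17 evaluable per group, 20% loss, 22 per group. The correlation r between baseline and follow-up score is not given. I assume 0.3 to 0.7, with equal SDs at both times.

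**The plan's own figure.** For a balanced one-way ANOVA the noncentrality is λ = k·n·f². With k = 2, f = 0.5 and 80% power, n = 16.7147 per group, which reproduces the stated value. Then 17/(1 − 0.2) = 21.25, so 22 per group and 44 in total. For two equal groups f = d/2, so f = 0.5 corresponds to 1.0 SD. The stated 0.8 SD is f = 0.4, which needs n = 25.52 per group. Both differences are therefore shown below.

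**Power of the three analyses.** With n per arm, λ = (n/2)·d²/v. The variance factor v is:

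- t-test on follow-up values: v = 1, df = 2n − 2 = 32
- t-test on change: v = 2(1 − r), df = 32
- baseline-adjusted (ANCOVA): v = 1 − r², df = 2n − 3 = 31

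For n = 17 and d = 0.8, λ = 8.5 × 0.64/v = 5.44/v. At r = 0.5, v is 1, 1 and 0.75, so λ is 5.44, 5.44 and 7.25. At d = 1.0, λ = 8.5/v.

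| d | r | Follow-up | Change | Adjusted | Gain over better unadjusted test |
|---|---|---|---|---|---|
| 0.8 | 0.3 | 61.9% | 48.1% | 65.9% | 4.0 points |
| 0.8 | 0.5 | 61.9% | 61.9% | 74.2% | 12.3 points |
| 0.8 | 0.6 | 61.9% | 71.5% | 80.6% | 9.1 points |
| 0.8 | 0.7 | 61.9% | 83.1% | 88.6% | 5.5 points |
| 1.0 | 0.3 | 80.7% | 66.6% | 84.1% | 3.4 points |
| 1.0 | 0.5 | 80.7% | 80.7% | 90.3% | 9.6 points |
| 1.0 | 0.6 | 80.7% | 88.5% | 94.2% | 5.7 points |
| 1.0 | 0.7 | 80.7% | 95.4% | 97.7% | 2.3 points |

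The change score is the weaker unadjusted choice below r = 0.5 and the stronger one above it. The adjusted analysis exceeds both in every row.

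**In patients.** For 80% power at 0.8 SD, adjustment needs 23.3, 19.4, 16.7 and 13.6 per arm at r = 0.3, 0.5, 0.6 and 0.7. Follow-up values need 25.5 throughout, and change needs 35.3, 25.5, 20.6 and 15.7.

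These formulas assume a continuous outcome. They suit Fugl-Meyer and VAS, not the Ashworth, House or Zancolli gradings.

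**The case against.** Several stronger readings are tempting, and the documents do not support them.

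- *The plan throws the baseline away.* Tables 1 and 2 define outcomes as changes, so the t-test may well be run on change scores. What stands is that baseline is not a covariate and that the tested value is not stated.
- *The t-test or Mann-Whitney test is the only randomised comparison.* Between-arm tests are also planned for discrete variables.
- *Efficacy will be judged from significance within each arm.* A reader might infer this from the formal within-arm tests. The risk in such a rule is real: if both arms improve equally and each within-arm test has power p, exactly one is significant with probability 2p(1 − p), which is 50% at p = 0.5 and 32% at p = 0.8. But no section states such a rule, the stated aim is between-arm, and between-arm tests are planned. It is a reason to label these tests descriptive, not a fault in the decision rule.
- *Patients who miss a visit are dropped.* The article gives no missing-data rule, and that is commonly left to the analysis plan.
- *Limb type must be adjusted for.* It is recorded, but the choice of covariates is also commonly left to the analysis plan.

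Two objections carry weight. The unadjusted test is valid under randomisation, so this is a matter of efficiency and not of bias. And most of the gap between 62% and 80% comes from using f = 0.5 while stating 0.8 SD; at 1.0 SD the test on follow-up values already has 81%.

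That the analysis plan is not shown does not remove the point. The article does not merely leave the between-arm model open: it names an unadjusted test for that comparison and gives the longitudinal model a within-arm role.

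**Conclusion.** The point holds as one of efficiency. As written, no estimate of the randomised effect on the clinical scales uses baseline as a covariate, and the quantity tested between arms is left open between change and follow-up value. With 17 per arm, adjustment would add about 4 to 12 percentage points of power over the better unadjusted test at 0.8 SD, and about 2 to 10 at 1.0 SD. This rests on assumed correlations of 0.3 to 0.7, equal SDs at baseline and follow-up, and a continuous scale.

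A reader might infer that adjustment restores the planned 80% power at 0.8 SD. It does so only if the correlation is about 0.6 or more, which nothing in the article establishes. The mismatch between 0.8 SD and f = 0.5 is a separate issue and needs its own correction.

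**What to change.** For continuous scales, replace the between-arm t-test or Mann-Whitney test with one model fitted to both arms: 6- and 12-month scores on arm, visit, arm-by-visit and baseline score. ANCOVA at 12 months is a simpler alternative. Report the 12-month between-arm difference with its 95% CI as the treatment effect, with patients analysed in the arm to which they were allocated. Label the within-arm tests as descriptive.

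Limb type (functional or hygienic) may be added as a covariate if the sample allows. A longitudinal proportional-odds model for the ordinal scales is debatable at about 17 per arm and is not part of this recommendation.

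The cost is a change of wording in the Data analysis section. It needs no new data, visits or patients.

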## Discussion

This article presents a two-arm RCT designed to compare the outcomes of surgery for upper limb spasticity with those of botulinum toxin therapy in patients with post-stroke spastic sequelae. We shall compare the effects of functional and hygienic changes on quality of life, sleep quality, anxiety, depression, and fMRI-measured brain structure and activity at baseline and at 6 and 12 months of follow up. We shall also evaluate the health and care costs associated with each approach.

Botulinum toxin is currently the first-line choice for regional post-stroke spasticity of the upper limb [44]. However, surgery generally obtains good long-term outcomes, with a low rate of major complications, and there is a lack of comparative data on the effectiveness, safety, and economic cost of the two approaches. In a study of patients with stroke or TBI from the National Inpatient Sample database (2001–2012) treated with upper limb reconstructive surgery, Beutel et al. [45] reported that 80% of 730,000 new cases of stroke/year survived the acute episode, 76% of survivors developed spasticity, and 50% of spastic patients could benefit from surgery [46]. However, surgery was performed in only 2,132 patients over the 12-year study period, i.e., < 1% of suitable candidates for surgery, indicating that upper limb reconstructive surgery may be considerably under-prescribed in this patient population.

To our best knowledge, no clinical trial has been published that compares the efficacy of surgery with that of botulinum toxin therapy.

In 2023, our group published a systematic review on the surgical treatment of spastic upper limb [47]. We concluded that surgery is a useful, safe, and long-lasting option for post-stroke spastic upper limbs, although most patients in the review were candidates for hygienic improvements alone. However, the design and heterogeneous patient populations of the reviewed studies yielded only a low level of evidence. We also called for clinical trials to compare between surgery and botulinum toxin in the treatment of these patients.

We expect that surgery will achieve improvements in all study parameters. The aim is not to exclude either approach but rather to explore how their potential and indications might be integrated within a multidisciplinary treatment protocol in a complementary manner.

This research is set in the context of chronic diseases, aging, and functional/mobility limitations. The results can be expected to have a major impact, because the high prevalence of stroke and the severe associated disability mean that an enormous number of patients can benefit from improved treatment protocols, and a more rational use of resources would yield significant economic benefits for health and care systems.

We anticipate that the findings of this RCT will contribute to our understanding of the role of upper limb surgery for spasticity in combination with conventional therapy. They will also provide evidence on the specific target group of patients who could gain most from surgery and on the safest and most appropriate procedures to consider. Future results will be communicated through articles in high-impact journals and international conferences on traumatology, rehabilitation and neurology.

The RCT design is a major strength of this study. On the other hand, it will be limited to a specific geographical area and to the public health sector, which may hinder the extrapolation of results to other populations. Other expected limitations include the heterogeneous nature of stroke patients in terms of their baseline injury and upper limb sequelae. In addition, the surgery will not be a single procedure but will involve different steps according to the needs of the patient, making analysis more complex. Multivariate analysis of the applied techniques may be required. The quality of life and psychosocial repercussions are not the only variables that could be selected, and functional and quality of life outcomes are influenced by environmental conditions and patient characteristics such as tiredness, cognitive level, and expression ability. Exclusion criteria have been selected to minimize these influences. Economic analyses may also over- or under-estimate costs, and it can be highly challenging to quantify all informal, secondary, or indirect costs. Nevertheless, information on the economic impact of diseases and their treatments is crucial for health policy planning and evaluation.

## Trial status

This paper is based on protocol version 2, dated 10 December 2022. Recruitment to the study began on 9 January 2023. Approximate date of recruitment completion: June 2025. The trial is registered on Clinical Trials.gov with the registration number NCT06392633.

## Abbreviations

ISCIII: Instituto de Salud Carlos III
RCT: Randomized Clinical Trial
fMRI: Functional Magnetic Resonance Imaging
CCP: Child Cerebral Palsy
TBI: Traumatic Brain Injury
HRQOL: Health- Related Quality of Life
VAS: Pain Visual Analogue Scale
PSQI: Pittsburgh Sleep Quality Index
HADS: Hospital Anxiety and Depression Scale
CSCUH: Clínico San Cecilio University Hospital
CJUH: Ciudad de Jaén University Hospital
ASA: Anesthetic Risk Scale
LMWH: Low-molecular weight heparin
t0: Baseline
t1: 6 months follow- up
t2: 12 months follow- up
FAC: Functional Ambulation Classification
